## Abstract

**Background**: Stroke is the leading cause of physical disability in adults in Catalonia. Despite this, there is a lack of evidence of physiotherapy interventions on functional capacity during the chronic phase of the pathology. This multicenter clinical trial will be conducted with a sample size of 75 participants. **Objectives**: The objective of the study is to evaluate the effectiveness of a therapeutic exercise program in physiotherapy using telerehabilitation to optimize functional recovery and quality of life in people with chronic stroke, and to determine its impact on adherence to the exercise program. **Methods**: This is a multicenter randomized controlled trial. Three parallel groups will be compared, and two will undergo the same type of therapy. A control group (CG) will perform conventional intervention in primary care. There will be two experimental groups; (EG1) will perform document-guided therapeutic exercises at home and (EG2) will perform therapeutic exercises at home guided by a telerehabilitation program. The outcomes to be measured are degree of independence of a person in their activities of daily living, assessed by the Barthel Index, motor function, muscle tone of the affected limbs, muscle strength of the affected limbs, balance, gait efficiency, perception of musculoskeletal pain, perception of fatigue, risk of falls, perception of quality of life, and the perception of perceived subjective change after treatment. These outcomes will be evaluated at baseline (T0), at ten weeks (T1) (end of the intervention), and at 18 weeks (T2). The study duration per patient will be 18 weeks (a ten-week intervention, followed by an eight-week intervention follow-up). The analysis will be performed using a mixed linear model (ANOVA 3X3) and significance level *p* < 0.05.

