### 2.2. Recruitment and Blinding

Participants will be randomly assigned to one of the three intervention groups using a computer-generated sequence through Random.org. To ensure allocation concealment, only the principal investigator (PI) will have access to the randomization list. This allocation will take place after obtaining informed consent, but before baseline assessments (T0), and the allocation will not be disclosed to the physiotherapists or outcome assessors until the participant has been formally enrolled in the study.

Although no stratification or block randomization procedures were applied, rigorous measures have been implemented to minimize potential bias and ensure the internal validity of the study. Outcome assessments will be performed by independent, previously trained physiotherapists acting as blinded assessors. In addition, statistical analyses will be conducted by researchers blinded to group allocation, thereby strengthening the objectivity of the results. All data will be recorded in a secure digital system, password-protected and accessible only to authorized members of the research team.

Prior to the randomization process, participant recruitment will follow a series of steps designed to ensure ethical transparency and informed understanding. First, the principal investigator, together with the physiotherapist responsible for each assigned center, will provide detailed information to collaborating healthcare professionals regarding the inclusion and exclusion criteria, as well as the general characteristics of the study. Second, physiotherapists from the research team will contact potential participants by phone through their primary care center to explain the purpose, design, duration, and potential risks and benefits of the study. If a patient expresses interest, a face-to-face appointment will be scheduled to provide more detailed information and resolve any questions. Informed consent will be obtained during this appointment, prior to accessing the participant’s medical history, in compliance with ethical standards and data privacy regulations.

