After group allocation and before starting treatment (T0), pre-intervention tests will be conducted to assess the baseline values of the primary and secondary outcome measures. A maximum of one week after completion of the intervention (T1), data will be collected for all efficacy outcomes (see Section 2.5). The same data will be collected two months after the end of the intervention (T2) (Figure 1). During the ten weeks of intervention, data will be collected in each session regarding adherence to the intervention (number of sessions and duration), intensity, exercises performed by each patient, and any incidents. All visits and efficacy evaluations will be conducted at the patient’s reference primary care center with the corresponding evaluating physiotherapist.

The study uses a single-blind design due to the nature of the interventions; therapists and participants cannot be blinded to treatment allocation. To avoid detection bias, efficacy outcomes will be assessed by an independent, blinded evaluator. Each center has a trained physiotherapist assessor, supervised by the principal investigator. The training information is available online and in paper format. Additionally, all statistical analyses will be conducted by researchers blinded to group allocation.

All data will be recorded in an online document shared by all the evaluators of the research team. A form created in a spreadsheet will be used. All researchers are trained in the use of the scales and the document, and they have a help guide, as well as a consultation service directly with the principal investigator of the study who is responsible for the logistics of the study. Access to the study registration document is restricted to authorized study personnel via password.

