### 2.3. Sample Size

The sample size was calculated using an a priori power analysis conducted with G*Power software (version 3.1.9.7). The calculaion was based on a mixed-design repeated-measures ANOVA with one between-subjects factor (three groups) and one within-subjects factor (three time points). A conservative medium effect size (f = 0.32) was selected for the calculation, which represents a smaller effect than that reported by Aphiphaksakul et al. [31], who reported functional improvements following a mobili-application-based training protocol in stroke patients. This effect size corresponds to an expected between-group difference of approximately 8–10 points on the Barthel Index, substantially exceeding the established MCID of 1.85 [32,33], thereby ensuring clinically meaningful differences. The analysis employed a significance level of α = 0.05 and a statistical power of 0.80 (1 − β = 0.80), and 10% dropout rate. Based on these parameters, the required sample size was determined to be 75 participants, with 25 participants allocated to each group.

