### 2.8. Statistical Analysis

The statistical analysis will be performed with the IBM SPSS v.26.0 software. Descriptive statistics will be calculated for all variables. To check the normal distribution of the variables, the Kolmogorov–Smirnov test with the Lilliefors correction will be used. For the comparison of the groups, a mixed 3 × 3 ANOVA will be carried out with interaction time (three measurement time points) and group (three intervention groups). The assumption of sphericity will be checked by means of the Mauchly test; if it is not met, the Greenhouse–Geisser correction will be used for interpretation.

The primary outcome and the Key Secondary Outcomes (motor function, muscle tone, muscle strength, balance, and quality of life) will be analyzed following this main model, given their clinical relevance. Additional Secondary Outcomes (gait performance, perceived pain, fatigue, fall risk, and subjective perceived change) will be analyzed using the same statistical approach but interpreted with greater caution due to their supplementary nature.

When a statistically significant effect is observed, the post hoc test will be performed using the Bonferroni correction to adjust for multiple comparisons. This correction will be applied systematically to all post hoc analyses to address the multiplicity of secondary outcomes.

For qualitative variables, the Chi-square test or Fisher’s Exact statistic will be used. The effect size will be calculated using Cohen’s d. Cohen’s coefficients [53] are interpreted as follows: large effect sizes, d > 0.8; moderate effect sizes, d = 0.5–0.79; and small, d = 0.2–0.49. The significance level was established at *p* < 0.05 with a 95% confidence interval. Missing data will be handled using Little’s MCAR test and multiple imputation (MICE) performed separately for each intervention group using the SPSS multiple imputation module. The analysis will be undertaken on an “intent-to-treat” basis.

Adherence outcomes (percentage of sessions completed, weekly frequency, and session duration) will be analyzed descriptively and compared between groups. If appropriate, exploratory analyses (e.g., correlation or regression models) will be conducted to examine the potential mediating or moderating role of adherence in relation to functional outcomes.

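### The 3 × 3 ANOVA treats T0 as an outcome level rather than a covariate: a valid test, but about 10 power points weaker at a T0–T1 correlation of 0.5, with little loss at 0.7 or above

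*Protocol article*

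**What the plan says.** Section 2.8 (Statistical Analysis) compares the groups by a mixed 3 × 3 "ANOVA will be carried out with interaction time (three measurement time points) and group (three intervention groups". The Barthel Index and the key secondary outcomes "will be analyzed following this main model, given their clinical relevance", and the additional secondary outcomes use the same approach. The Abstract fixes the time points: "These outcomes will be evaluated at baseline (T0), at ten weeks (T1) (end of the intervention), and at 18 weeks (T2". T0 is therefore one level of the time factor. No baseline covariate and no constraint of equal arm means at T0 is mentioned.

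Section 2.3 (Sample Size) uses the same layout, a "mixed-design repeated-measures ANOVA with one between-subjects factor (three groups) and one within-subjects factor (three time points", and the effect size is given as "A conservative medium effect size (f = 0.32) was selected for the calculation". Section 2.2 (Recruitment and Blinding) says that "no stratification or block randomization procedures were applied". It also says that, once groups have been allocated and before treatment starts, "pre-intervention tests will be conducted to assess the baseline values of the primary and secondary outcome measures".

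**The concern.** With T0 as a free outcome level, the model estimates arm differences at T0 that randomization allows only by chance, and the treatment effect is read as a departure from those estimates. This gives the T0 value a fixed weight of one. When T0 and T1 are imperfectly correlated, that weight is too large, and the chance T0 difference adds noise to the contrast. A covariate lets the data set the weight.

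The design does nothing to limit the chance difference. With 25 per arm and simple randomization, its standard error between two arms is √(2/25) = 0.28 SD. At stake is precision for the Barthel Index and for every secondary outcome that has a T0 value, in a trial too small to give precision away.

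**Working it through.** **Inputs.** From Section 2.3: f = 0.32, α = 0.05, power 0.80, dropout 10%, N = 75 in three equal arms. Assumed: the same correlation ρ between all pairs of visits (the article states none), equal variances, no effect at T0, and f = 0.32 at both T1 and T2.

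**The plan's own figure.** The repeated-measures between-factors calculation has λ = f²·N·3/(1+2ρ). With ρ = 0.5 and N = 66, λ = 0.1024 × 66 × 3/2 = 10.14 on 2 and 63 df, and power is 80.1%; N = 65 gives 79.4%. Then 66/0.9 = 73.3, so 74, or 75 for equal arms. The interaction calculation with the SPSS-type effect size, λ = f²(N−3)·2 = 12.90 on 4 and 126 df, gives 82% at N = 66 and is also consistent with 75. The default interaction option at ρ = 0.5 needs only 24 and does not reproduce the figure. The stated N is therefore reproducible, but not in a way that reveals the intended ρ for the group × time test.

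**Variance at one visit.** Change from T0 has variance proportional to 2(1−ρ); T1 adjusted for T0 has 1−ρ². The ratio is (1−ρ²)/[2(1−ρ)] = (1+ρ)/2, which is 0.75, 0.85 and 0.90 at ρ = 0.5, 0.7 and 0.8.

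**Noncentrality.** The effect profile over time is (0, 1, 1). Centred, it is (−2/3, 1/3, 1/3), with sum of squares 2/3.

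- A. Planned group × time test: λ = N·f²·(2/3)/(1−ρ), on 4 and 2(N−3) df.
- B. T1 adjusted for T0: λ = N·f²/(1−ρ²), on 2 and N−4 df.
- C. Change T1−T0, no covariate: λ = N·f²/[2(1−ρ)], on 2 and N−3 df.
- D. Mean of T1 and T2 minus T0, no covariate: the variance factor is (1+ρ)/2 + 1 − 2ρ = 1.5(1−ρ), so λ is the same as in A, on 2 and N−3 df.
- E. Mean of T1 and T2 adjusted for T0: λ = N·f²/[(1+ρ)/2 − ρ²], on 2 and N−4 df.

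For example, at N = 75 and ρ = 0.5, N·f² = 7.68, so λ is 10.24 for A, 10.24 for B, 7.68 for C, 10.24 for D and 15.36 for E.

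**Power with 75 analysed**

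| ρ | A planned, 4 df | B adjusted T1 | C change T1 | D change of mean | E adjusted mean |
|---|---|---|---|---|---|
| 0.5 | 71% | 81% | 68% | 81% | 94% |
| 0.6 | 82% | 87% | 78% | 89% | 96% |
| 0.7 | 92% | 94% | 89% | 96% | 99% |
| 0.8 | 99% | 99% | 98% | 99.6% | 99.9% |

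With 66 analysed, A against B is 65% and 75% at ρ = 0.5, 76% and 82% at 0.6, 88% and 90% at 0.7, and 98% and 97% at 0.8. A simulation at ρ = 0.5 with 22 per arm gave 65% and 74%.

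**Separating the causes.** C against B isolates the covariate at T1: 13 points at ρ = 0.5, 9 at 0.6, 4 to 5 at 0.7 and 1 at 0.8. A against D isolates the use of 2 rather than 4 df: 10 points at ρ = 0.5. A against B mixes the two, because A also uses T2. At ρ = 0.5 A and B have the same λ, and the 10-point gap reflects the degrees of freedom.

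**Error rate.** A T0-adjusted model read visit by visit yields 3 arm pairs × 2 visits = 6 contrasts. Unadjusted, a null simulation with 25 per arm gives about 22% familywise error at ρ of 0.5 to 0.8.

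**The case against.** The planned test holds its level, matches the layout on which the trial was sized, and contradicts nothing in the article. Under randomization, chance imbalance at T0 adds variance, not bias. All of this stands.

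The correlation is unknown and may be high. Participants are more than six months past their stroke, and the Conclusions describe such patients as clinically stable. At ρ = 0.8 nothing is lost against adjusted T1. This also stands, and it limits the size of the point. The power figures are illustrative in another respect: the Barthel Index stops at 100 and scores under 60 are excluded, so normal theory with equal correlations is an approximation.

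Having T0 among the outcomes is not inefficient in itself. A longitudinal model that constrains the arm means to be equal at T0 recovers the precision of covariate adjustment. The ANOVA described has no such constraint.

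T0 is taken after allocation, and Section 2.2 says that participants cannot be blinded. If they know their arm at T0, the baseline may not be clean. Assessor blinding reduces the risk, and a change-based contrast needs the same assumption, so this is no reason to prefer the current model. It does need a sentence in the plan.

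A reader might infer that the planned analysis is biased, or that it loses 10 points or more whatever the data. The article supports neither: the first is contrary to randomization, and the second requires ρ of about 0.5 or less in the comparison with adjusted T1. A reader might also credit the whole rise from 71% to 94% at ρ = 0.5 to the covariate. About 10 of those 23 points come from pooling T1 and T2 in a 2-df test, which is a separate choice.

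**Conclusion.** The point holds as one of efficiency, not validity. The analysis in Section 2.8 is less precise than adjustment for T0 by the factor (1+ρ)/2 in variance at a single visit. At the plan's f = 0.32 with 75 analysed, T0-adjusted T1 gains about 10 power points over the planned test at ρ = 0.5, about 5 at 0.6, 1 to 2 at 0.7 and none at 0.8. At ρ = 0.5 the planned test falls short of the 80% target even without dropout (71%). These figures rest on an assumed, equal correlation between visits and on an effect of the same size at T1 and T2. The change is worth making because the T0 values are collected anyway, but the expected gain should not be stated without its dependence on ρ.

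**What to change.** In Section 2.8, replace the 3 × 3 ANOVA by a model of the T1 and T2 values with group, visit, group × visit and the participant's T0 value as covariate (SPSS MIXED). Use it for the Barthel Index and for every other outcome that has a T0 value.

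Name one overall test as primary: the 2-df baseline-adjusted group effect, either averaged over T1 and T2 or at T1. Keep the plan's Bonferroni correction for the pairwise arm contrasts by visit that follow, counting every contrast that is read (six if both visits are used). Without these two steps the change would not be free in error rate.

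State that the T0 assessors are blinded and that T0 is obtained before participants learn their arm; if the latter cannot be ensured, acknowledge the assumption.

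Cost: wording only, with no extra patients, visits or data. The power statement in Section 2.3 refers to the ANOVA and should be described as such once the analysis model differs.

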### 2.5. Outcome Measure

Descriptive data of the sample will be recorded, as well as anthropometric data and various assessment measures for the following evaluation variables.

The primary outcome is the degree of dependence or functional capacity for activities of daily living, which is assessed using the Barthel Index [32], and it is the validated scale used for the sample calculation [31].

The secondary outcomes have been classified into two categories: (1) Key Secondary Outcomes, which include motor function, muscle tone, muscle strength, balance, and quality of life, and (2) Additional Secondary Outcomes, which include gait performance (gait pattern and gait speed), perceived pain, fatigue, fall risk, subjectively perceived change after treatment, and adherence to the exercise program.

The secondary variables and their respective evaluation tools are as follows: motor function will be assessed using the Modified Motor Assessment Scale; muscle tone of the affected limbs will be measured with the Modified Ashworth Scale; muscle strength of the affected limbs will be evaluated using the Medical Research Council scale; balance will be assessed with the Postural Assessment Scale for Stroke Patients; walking efficiency will be measured using the Wisconsin Gait Scale and the 4 Meter Gait Speed Test; perception of osteomuscular pain will be evaluated through the Brief Pain Inventory; perception of fatigue will be measured using the Fatigue Severity Scale; fall risk will be assessed with the Time Up and Go Test; quality of life perception will be evaluated using the Newcastle Stroke-Specific Quality of Life Measure (Spanish version); and perception of subjective change post-treatment will be measured with the Global Rating of Change Scale (Table 1).

Adherence, included as an Additional Secondary Outcome, will be quantified as the proportion of prescribed sessions completed, the weekly frequency achieved, and the duration of each session, allowing further analysis of its potential influence on the functional outcomes observed across the intervention groups.

Although this broad set of outcomes aims to provide a comprehensive clinical profile of participants, the assessment burden is minimized through efficient scheduling of evaluation visits, grouping compatible measures within the same session, and using validated instruments with short administration times.

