The Fatigue Severity Scale (FSS) evaluates the severity of fatigue and its impact on daily activities, with scores ranging from 1 (strongly disagree) to 7 (strongly agree). The FSS is highly reliable for monitoring fatigue in stroke rehabilitation [44].

The Timed Up and Go (TUG) Test assesses fall risk by timing how long it takes for a patient to stand up from a chair, walk 3 m, turn, return, and sit down. The TUG test is a reliable and valid measure for fall risk [45].

The Newcastle Stroke-Specific Quality of Life Measure (NEWSQOL) evaluates stroke-specific quality of life, encompassing physical, emotional, social, and cognitive domains. It has demonstrated high internal reliability and strong construct, concurrent, and predictive validity [46].

The Global Rating of Change Scale (GROC) measures the patient’s perception of changes in their health or functioning after an intervention. It demonstrates strong test–retest reliability and robust concurrent and construct validity [47].

Information regarding stroke diagnosis, medical history, and stroke onset will be collected from patient records in the ECAP programs (ICS). Additionally, data on participant characteristics, including sex, age, family support, primary caregiver involvement, medication use, comorbidities, dysphagia, lesion location and side, time post-stroke, and stroke severity (assessed by the NIHSS and modified Rankin Scale), will be gathered for comprehensive analysis.

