An abnormal increase in muscle tone is also an important condition to assess, using the Modified Ashworth Scale (MAS), as patients may experience spasticity in the muscles affected by brain injury, which can complicate the recovery of mobility and motor function. Additionally, the muscle strength of the four limbs will be measured using the Medical Research Council scale. The evaluation will have clinical relevance if the results show score changes of 2 points for the MMAS [54], and between 0.45 and 0.73 points in the lower extremities and between 0.48 and 0.76 points in the upper extremities for the MAS [55].

Gait difficulties are among the most common physical impairments after a stroke. The gait pattern is characterized by being asymmetric, with reduced speed and shortened stride length, which generally requires high energy expenditure. Improvement of the parameters will be considered when there is an increase of 2.5 points on the WGS scale [56], and approximately 0.09 m/s increase in baseline speed on the 4MWT [42]. Balance training, both dynamic and static, becomes essential to improving core functionality, as well as performing therapeutic exercises that consider the biomechanics of the trunk and lower limbs for potential improvement in gait quality. For its evaluation, the Postural Assessment Scale for Stroke Patients (PASS) and the Timed Up and Go (TUG) test have been chosen to assess fall risk. A positive evaluation at the end of the study will be considered if there is an improvement of 3 points on the PASS [57] scale and a change from 1.0 to 1.5 s in the TUG [58].

Assessing parameters that affect the daily lives of post-stroke patients is also highly relevant for evaluating the effectiveness of the study, such as measuring the perception of musculoskeletal pain using the Brief Pain Questionnaire and the perception of fatigue using the Fatigue Severity Scale.

It is also necessary to evaluate participation outcomes and quality of life [59]. Therefore, the scales used to measure the perception of quality of life will include NewsQol, and the Global Rating of Change Scale will be used to measure the perceived subjective change post-intervention.

The scales selected to evaluate the variables in this study have demonstrated good reliability and validity in stroke populations [60].

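### The Global Rating of Change is assigned to the mixed 3 × 3 ANOVA over T0, T1 and T2, but a rating of change after treatment has no valid T0 value

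*Protocol article*

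**What the plan says.** Section 2.8 sets one main model: "a mixed 3 × 3 ANOVA will be carried out with interaction time (three measurement time points) and group (three intervention groups"). It then extends that model by name: "Additional Secondary Outcomes (gait performance, perceived pain, fatigue, fall risk, and subjective perceived change) will be analyzed using the same statistical approach". The only qualification is that these results will be read more cautiously. Adherence gets its own paragraph and a different treatment; perceived change does not.

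The instrument and its meaning are given in three places:

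- Section 2.5: "perception of subjective change post-treatment will be measured with the Global Rating of Change Scale".
- Assessments subsection: the scale "measures the patient’s perception of changes in their health or functioning after an intervention".
- Discussion: "the Global Rating of Change Scale will be used to measure the perceived subjective change post-intervention".

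Two statements on timing cover all outcomes together. After a list that includes perceived change, the Abstract says: "These outcomes will be evaluated at baseline (T0), at ten weeks (T1) (end of the intervention), and at 18 weeks (T2"). Section 2.2 says that before treatment "pre-intervention tests will be conducted to assess the baseline values of the primary and secondary outcome measures". Neither makes an exception for the Global Rating of Change.

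**The concern.** A 3 × 3 mixed ANOVA needs a score for each participant at each of three visits. By the article's own definition, a rating of change after treatment does not exist before treatment. The article therefore names a model for this outcome that cannot be filled with meaningful data, and it gives no rule for the empty level.

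Without a rule, the analyst has to invent one after the data are in: leave T0 blank, code it as zero, or ask patients at baseline about change over some unspecified earlier period. These choices give different tests with different meanings. What is at stake is the interpretability of the trial's only global patient rating of change.

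**Working it through.** **Inputs from the article.** Three groups of 25, N = 75 (Sections 2.1 and 2.3). Three time levels, with Greenhouse–Geisser correction where sphericity fails, and multiple imputation by group (Section 2.8). The article gives no numerical figure for this outcome, so there is nothing to reproduce. The question is whether a T0 level exists, and the definitions quoted above say that it does not.

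**Option 1: T0 left blank.** Every participant lacks one of the three repeated measures. Under listwise deletion the number analysable is 75 − 75 = 0. Imputation by group has 0 observed T0 values in each group of 25, so there is nothing to fit an imputation model to.

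**Option 2: T0 set to zero.** Let group A have mean a and group B mean b at both T1 and T2, with d = a − b.

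- Interaction contrast, T0 to T1: (a − 0) − (b − 0) = d.
- Interaction contrast, T1 to T2: (a − a) − (b − b) = 0.

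The whole interaction comes from the placeholder. A steady group difference, with no change between T1 and T2, is reported as a group-by-time interaction. Likewise, any common improvement m at T1 and T2 gives a time contrast of m − 0 = m against a number nobody reported.

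**Option 3: patients actually asked at T0.** They would rate change over a period that the article does not define, which is a different quantity from the ratings at T1 and T2.

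**Size of the effect under option 2.** Simulation with 4,000 trials per scenario and 25 per group. The following are assumptions, not figures from the article: SD 1, a common mean of 1 at T1 and T2, one group shifted by 0 or 0.8 SD at both visits, and T1–T2 correlation of 0.5 or 0.8. Entries are the percentage of trials with p < 0.05.

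| Correlation | Shift | 3 × 3 interaction (Greenhouse–Geisser) | 3 × 2 interaction | Group effect, 3 × 3 | Group effect, 3 × 2 |
|---|---|---|---|---|---|
| 0.5 | 0 | 5.2 | 4.7 | 5.2 | 5.2 |
| 0.8 | 0 | 4.7 | 5.5 | 4.9 | 4.9 |
| 0.5 | 0.8 | 86.0 | 5.1 | 91.6 | 91.6 |
| 0.8 | 0.8 | 85.7 | 4.5 | 86.7 | 86.7 |

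With a constant difference, the 3 × 2 model shows it as a group effect and finds no interaction beyond chance. The 3 × 3 model also shows it as an interaction. With no difference, the corrected 3 × 3 interaction test stays near its nominal 5%.

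**After correction.** With T1 and T2 only, the time factor has 2 − 1 = 1 degree of freedom and the interaction (3 − 1)(2 − 1) = 2, against 2 and 4 in the stated model. Mauchly's test is not needed with two levels.

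**The case against.** The best defence is that the T0 scheduling comes from summary sentences. Read literally, the Section 2.2 sentence would also demand a baseline value for adherence, another secondary outcome, which is impossible. The article repeatedly calls this rating post-treatment, so the natural reading is T1 and T2 only, and a schedule by instrument may sit in the full protocol. That weakens the scheduling half of the point. It does not rescue the analysis: Section 2.8 names perceived change under the three-time-point model, and an analysis plan that restricted it to T1 and T2 would have to depart from that sentence. The provision for chi-square tests on qualitative variables does not help either, because perceived change is listed under the ANOVA.

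A second defence is that the Abstract describes the analysis as a mixed linear model. Fitted that way, participants keep their T1 and T2 records. This is correct, so the loss of all 75 participants is conditional on blank T0 values and listwise deletion. But the T0 cells remain inestimable, and the model reduces to 3 × 2, which is the correction proposed here.

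A reader might also infer three stronger things about coding T0 as zero. None is supported.

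- *That sphericity must fail.* Sphericity concerns the variances of differences between visits. With T0 = 0 and unit variance at T1 and T2, these are 1, 1 and 2 − 2ρ, where ρ is the T1–T2 correlation. At ρ = 0.5 all equal 1 and sphericity holds exactly. Elsewhere the departure is moderate (epsilon 0.95 at ρ = 0.3, 0.91 at 0.7, 0.80 at 0.8), and the planned correction covers it.
- *That the group effect loses a third.* The marginal difference does become (0 + d + d)/3 = 2d/3. Each participant's mean also becomes (T1 + T2)/3, two thirds of (T1 + T2)/2, so the error shrinks by the same factor. F, p and the standardised difference do not change; the two group-effect columns above are identical.
- *That false positives between groups increase.* The corrected interaction test rejects in 4.7–5.2% of trials under no effect. A time effect against zero says only that average perceived change differs from zero; it leads to comparisons between visits and does not by itself bear on the groups.

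**Conclusion.** The point holds. The article assigns the Global Rating of Change to a model with a T0 level, defines the scale so that no T0 value exists, and gives no exemption. This is a stated rule that does not fit the outcome, not a detail left to another document.

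The consequence is an analysis that is empty (T0 blank with listwise deletion) or one whose time and interaction terms refer to an invented baseline (T0 coded zero). It is a problem of definition and interpretation, not of inflated type I error. The 86% against 4–5% contrast illustrates how a constant difference is relabelled as an interaction. It rests on the assumed SD, correlations and 0.8 SD shift, but the algebra behind it does not.

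The reach is small: one of the 13 rows in Table 1 (1 primary, 5 key secondary, 7 additional), in the tier already marked for cautious reading. The primary outcome, the key secondary outcomes and the sample size are unaffected. It should be corrected because the correction is almost free.

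**What to change.** In Sections 2.2 and 2.5, state that the Global Rating of Change is collected at T1 and T2 only. In Section 2.8, take it out of the 3 × 3 model and state that the groups will be compared on it using T1 and T2, either in a 3 × 2 model or by a between-group comparison at each visit. Say which of the two applies before the data are analysed. If the response format calls for it, use a rank-based or ordinal method; the article does not give the format, so the choice can be left open on that ground alone. The Abstract's sentence on time points needs a matching exception.

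The cost is about one sentence in each section and one form fewer at T0, with no change to the sample size, the visits or any other outcome.
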